## Abstract

**Background:**

Results of previous studies have shown that exercise training can improve cognitive functions in healthy older people. Some studies have demonstrated that long-term combination exercise training can facilitate memory function improvement better than either aerobic or strength exercise training alone. Nevertheless, it remains unclear whether short-term combination exercise training can improve diverse cognitive functions in healthy older people or not. We investigate the effects of four weeks of short-term combination exercise training on various cognitive functions (executive functions, episodic memory, short-term memory, working memory, attention, reading ability, and processing speed) of healthy older people.

**Methods:**

A single-blinded intervention with two parallel groups (combination exercise training; waiting list control) is used. Testers are blind to the study hypothesis and the participants’ group membership. Through an advertisement in a local newspaper, 64 healthy older adults are recruited and then assigned randomly to a combination exercise training group or a waiting list control group. Participants in the combination exercise training group must participate in the short-term combination exercise training (aerobic and strength exercise training) three days per week during the four weeks (12 workouts in total). The waiting list group does not participate in the combination exercise training. The primary outcome measure is the Stroop test score: a measure of executive function. Secondary outcome measures are assessments including the Verbal Fluency Task, Logical Memory, First and Second Names, Digit Span Forward, Digit span backward, Japanese Reading Test, Digit Cancellation Task, Digit Symbol Coding, and Symbol Search. We assess these outcome measures before and after the intervention.

**Discussion:**

This report is the first of a study that investigates the beneficial effects of short-term combination exercise training on diverse cognitive functions of older people. Our study is expected to provide sufficient evidence of short-term combination exercise’s effectiveness.

**Trial registration:**

This trial was registered in The University Hospital Medical Information Network Clinical Trials Registry (Number UMIN000007828).

## Background

Cognitive functions decline with age. For instance, older people might experience a decline in several cognitive functions such as memory [1], attention [2], executive functions [3,4], and processing speed [5]. Decline in cognitive ability engenders difficulty in performing basic daily living activities [6,7]. Consequently, maintaining or improving cognitive function in older adults is drawing increasing attention [8-15].

Previous studies have demonstrated that physical exercise training can improve cognitive functions in the healthy older people [14-20]. Physical exercise training can be of two types: aerobic exercise training and strength exercise training [18]. Aerobic exercise training is defined as structured exercise programs involving the use of large muscle groups for extended periods of time in activities that are rhythmic in nature, including but not limited to walking, stepping, running, swimming, cycling, and rowing [21]. Strength exercise training uses resistance against the force of muscular contraction to build strength, anaerobic endurance, and skeletal muscle mass. Strength exercise training often uses gravity to oppose muscle contraction [19,22,23]. Previous studies using randomized controlled trials (RCT) have revealed that aerobic exercise training alone and strength exercise training alone improved memory in healthy older people [22-24].

Some previous reports have described that combination exercise training, which combines exercise training of various types (for example, aerobic and strength exercise training) can also facilitate improvement of cognitive functions [20,21,25]. Williams and Lord [26] investigated whether combination exercise training for 42 weeks could improve cognitive functions in healthy adults or not. Results showed that the combination exercise training group improved processing speed and memory. Lautenschlager *et al*. [27] investigated the beneficial effects of 24 weeks of combination exercise training on the cognitive functions of older people with Alzheimer disease. The results showed that the combination exercise training group, which performed walking and strength exercise training, exhibited more significant improvement than a control group, which received educational classes, in the Alzheimer Disease Assessment Scale (ADAS) and word recall tests. Moreover, a meta-analysis showed that combination training had a larger effect than aerobic exercise training alone [14]. Consequently, combination exercise training appears to be the most effective exercise training for improving cognitive function.

### Purpose of this study

Although earlier studies showed that long-term (>24 weeks) combination exercise training can improve memory functions in elderly people [14,20,21,25,26], unresolved issues remain. First, it remains unclear whether or not short-term combination exercise training, for example, four weeks, can improve cognitive functions in healthy older people. Second, it is unclear whether the combination exercise training can improve diverse cognitive functions (for example, executive functions and attention) in healthy older people or not. Consequently, this study was conducted to investigate whether four weeks of combination exercise training can improve diverse cognitive functions in healthy older people or not. To reveal the beneficial effects of combination exercise training on widely various cognitive functions, we conduct a single-blinded RCT. Testers are blinded to the study hypothesis and the group membership of participants. We assess a broad range of cognitive functions. The measured cognitive functions are divisible into seven categories: executive functions, episodic memory, short-term memory, working memory, reading ability, attention, and processing speed.

## Method

### Randomized controlled trial design and setting of this trial

This study, which was registered in the University Hospital Medical Information Network (UMIN) Clinical Trial Registry (UMIN000007828), is an RCT conducted in Sendai city, Miyagi prefecture, Japan. Written informed consent to participate in the study will be obtained from each participant before enrollment. The protocol of this study and informed consent were approved by the Ethics Committee of the Tohoku University Graduate School of Medicine.

To assess the impact of short-term combination exercise on diverse cognitive functions in healthy older people, we use a single-blinded intervention with two parallel groups: a combination exercise training group and a waiting list control group. Testers are blind to the study’s hypothesis and the group membership of participants. The Consolidated Standards of Reporting Trials (CONSORT) statement [28] (http://www.consort-statement.org/home/) was used as a framework for developing the study methodology (Additional file 1). The trial design is presented in Figure 1.

**Figure 1 F1:**
[figure not shown]
CONSORT flowchart.

### Recruitment and selection of participants

Participants are recruited from the general population through advertisements in the local town paper and local newspaper. Interested participants are screened using a semi-structured telephone interview. After the telephone interview, participants are invited to visit Tohoku University for a more detailed screening assessment and to provide written informed consent.

### Inclusion and exclusion criteria

The purpose of this intervention is to investigate the beneficial effects of combination exercise training on diverse cognitive functions in healthy older adults. Criteria include participants who report themselves as right-handed, native Japanese speakers, unconcerned about their own memory functions, not using medications known to interfere with cognitive functions (including benzodiazepines, antidepressants, and other central nervous system agents), and having no disease known to affect the central nervous system, including thyroid disease, multiple sclerosis, Parkinson disease, stroke, severe hypertension (systolic blood pressure over 180, diastolic blood pressure over 110), and diabetes. The age of participants is more than 60 years old. We elicit the above information using a semi-structured telephone interview and self-report questionnaire. We check blood pressure at the start of this intervention study.

There are two reasons why we include only right-handed people. First, previous studies showed the association of handedness with cognitive functions for older people [29]. Second, we will investigate the effects of the combination exercise training on brain structures or brain functions using neuroimaging techniques such as magnetic resonance imaging after this intervention. In the neuroimaging studies, we usually use only right-handed people because of differences of lateralization of brain functions between right- and left-handed people. Language is more likely to be lateralized differently in left-handed people than in right-handed people. It means that in right-handed people, language functions such as grammar and vocabulary are most likely to be dependent on brain regions in the left hemisphere [30]. On the other hand, in left-handed people, it is more likely that left and right hemispheric brain regions will be involved [30,31]. To minimize the influence of subclinical degenerative conditions, the following exclusion criteria are employed. Criteria exclude participants who have an Intelligence Quotient (IQ) less than 85 derived from the Japanese reading test (JART) [32], a score of Mini Mental Status Examination (MMSE) less than 26 [33], and a score of Frontal Assessment Battery at bedside (FAB) less than 12 [34]. MMSE [33] is the most widely used screening instrument for the detection of cognitive impairment in older adults. MMSE is a 20-item instrument. The items of MMSE measure orientation for place and time, memory and attention, language skills, and visuospatial abilities. MMSE is scored from 0 to 30. Lower scores of MMSE indicate greater degrees of general cognitive dysfunction. The primary measure is the total score of this task (max = 30). FAB [34] evaluates executive functions. FAB consists of six subtests, namely, those for similarities (conceptualization), lexical fluency (mental flexibility), motor series (programming), conflicting instructions (sensitivity to interference), go/no-go (inhibitory control), and prehension behavior (environmental autonomy). FAB is scored from 0 to 18. Lower scores of FAB indicate greater degrees of executive dysfunction. The primary measure is the total score of this task (max = 18). This criterion is the same as our previous study, which investigated the beneficial effects of cognitive training using video games for four weeks [13]. Participants who participate in other cognitive-related intervention studies or other exercise intervention studies will be excluded.

### Randomization

Randomization is designed to take place after receiving the informed consent statement. A researcher (RN), who has no contact with the study participants, assigns participants to either the combination exercise group or the waiting list group by a random allocation sequence. The random allocation sequence will be generated by the Microsoft Excel 2003 program with the RAND function with no blocks and restrictions. Letters are used to inform participants of their allocation.

### Intervention group (combination exercise training group)

The intervention group receives the following combination exercise training, which was developed by Curves (Curves Japan Co., Ltd.). The combination exercise combines training of three types (aerobic, strength, and stretching; http://www.curves.co.jp/consistency/program/). Participants perform the combination exercise training three days per week throughout the four weeks (12 workouts in total). Each circuit-style workout consists of 12 strength training exercises (chest press/seated row, squat, shoulder press/lateral pull, leg extension/leg curl, abdominal crunch/back extension, lateral lift, elbow flexion/extension, horizontal leg press, pectoral deck, oblique, hip abductor/adductor, gluteus; http://www.curves.co.jp/consistency/program/point01/). The strength training machines contain calibrated pneumatic resistance pistons that allow for opposing muscle groups to be trained in a concentric-only fashion. Participants are informed of the proper use of all equipment and are instructed to complete as many repetitions in a 30-s time period. In a continuous, interval fashion, participants perform floor-based aerobic training (for example, running/skipping in place, and arm circles) on recovery pads for a 30-s time period after each resistance exercise in an effort to maintain a consistent exercise heart rate corresponding to 60 to 80% of their maximum heart rate. All workouts are supervised by trained exercise instructors who assist with proper exercise technique and maintenance of adequate exercise intensity. Participants must complete two circuits (24 min). After two rotations, participants do standardized whole-body stretching training (6 min). The whole-body stretching training consists of 12 stretching exercises (Achilles' tendon, sole of the foot, thigh, armpit, shoulder, shoulder/upper arm, chest/arm, shoulder/chest/arm, waist, back of knee, base of thigh, back; http://www.curves.co.jp/consistency/program/point02/).

### Waiting list group (no combination exercise training group)

The wait-listed group receives no intervention. Those participants are informed by letter that they are scheduled to receive an invitation to participate after a waiting period of four weeks. We ask the wait-list group not to go to the gym or not to join exercise programs during the waiting period. The previous study [35] suggested that the wait-listed group tends to show a resentful demoralization and to withdraw from the study. Based on this suggestion, 1) we set a short-term waiting duration (four weeks) and 2) to keep the motivation to participate in this study, we will send a short letter to the wait-list group at the midpoint of the waiting duration. In this study, we use no active control group such as a stretch exercise training group alone or placebo group such as a social contact group because results of previous intervention reports describe that no difference exists in cognitive or functional improvement between the stretch exercise training group (active control group) and non-exercise control group (control group) [36] or between the social-contact group (placebo group) and no-social-contact groups (control group) [37,38]. Moreover, using the wait-list control group has the advantage of letting everyone in the study receive the new intervention such as the combination exercise training (sooner or later). Thus, we use the wait-list control group in this intervention study.

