### Sample size

Our sample size estimation is based on the change score in the reverse Stroop task, which is the primary outcome in this study. This study uses eta squared (η^*2*^) as an index of effect size. As a descriptive index of strength of association between an experimental factor (main effect or interaction effect) and a dependent variable, η^*2*^ is defined as the proportion of total variation attributable to the factor, and it ranges in value from 0 to 1 [52]. Using information (the sums of squares for total; SS total, the sum of squares for factor; SS factor) reported in an analysis of covariance (ANCOVA) summary table, we calculate η^*2*^ (SS factor divided by SS total). SS factor is the variation attributable to the factor and SS total is the total variation, which includes the SS factor and the sum of squares for error. In actuality, η^*2*^ ≥0.01 is regarded as a small effect, η^2^ ≥0.06 as a medium effect, and η^*2*^ ≥0.14 as a large effect [52]. We expect to detect a large effect size (η^2^ = 0.14) of the change score (post-training score minus pre-training score) in the reverse Stroop task between combination exercise and waiting list groups. The sample size was determined using G*power [53,54] based on 80% power, a two-sided hypothesis test, an alpha level of 5%, an ANCOVA model that includes a baseline reverse Stroop task score, age and sex as a covariate. The sample size calculation indicated that we need 32 participants in each of the combination exercise and waiting list groups with consideration of a 20% drop-out rate.

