### Analysis

This study is designed to evaluate the beneficial effect of the short-term combination exercise in older people. We calculate the change score (post-training score minus pre-training score) in all cognitive function measures. We conduct an ANCOVA for the change scores in each cognitive test. The change scores are the dependent variable. Groups (combination exercise, waiting list) are the independent variable. Pre-training scores in the dependent variable, sex, age categories are covariates to adjust for background characteristics and to exclude the possibility that any pre-existing difference of measure between groups affects the result of each measure. The level of significance is set as *P* <0.05. This study reports η^*2*^ as an index of effect size (please see the detail in Sample Size). Missing data are imputed using Missing Value Analysis in the Statistical Package for the Social Sciences (SPSS). In particular, we impute missing values using maximum likelihood estimation based on the expectation-maximization algorism with the observed data in an iterative process [55]. All randomized participants are included in the analyses in line with their allocation, irrespective of how many sessions they complete (intention-to-treat principle). All analyses are performed using the SPSS (version 18 or higher; SPSS Japan Inc.).

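### Only the waiting-list arm is asked to avoid gyms and exercise programmes, so outside exercise can differ by arm because of the instructions, by an amount the article does not determine

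*Protocol article*

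**What the plan says.** All references are to the protocol article.

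- **Waiting list group.** "The wait-listed group receives no intervention", and then: "We ask the wait-list group not to go to the gym or not to join exercise programs during the waiting period". The same section refers to a non-exercise control group when it explains why no active control is used.
- **Intervention group.** This section describes the 12 supervised workouts in detail. It says nothing about exercise outside them.
- **Inclusion and exclusion criteria.** The only criterion that concerns exercise is "Participants who participate in other cognitive-related intervention studies or other exercise intervention studies will be excluded". It covers concurrent trials, not a person's own gym or class attendance.
- **Recruitment.** "Participants are recruited from the general population through advertisements in the local town paper and local newspaper".
- **Randomization.** The sequence is "generated by the Microsoft Excel 2003 program with the RAND function with no blocks and restrictions", and participants learn their allocation by letter.
- **Analysis.** "Pre-training scores in the dependent variable, sex, age categories are covariates".
- **Sample size.** "We expect to detect a large effect size (η^2^ = 0.14) of the change score" in the reverse Stroop task, with 32 participants per arm.

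**The concern.** The restriction is given after allocation and, as the article is written, to one arm. A control who already goes to a gym is, on the plain wording, asked to stop for four weeks. A similar person in the exercise arm is told nothing in the article and could keep that exercise on top of the workouts. The Background section takes it that exercise improves cognition in healthy older people. On that premise, withholding outside exercise from one arm alone would tend to widen the difference in favour of the programme.

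What is at stake is the meaning of the comparison. A difference between arms could contain three things: the effect of the workouts, a loss among controls who paused their own exercise, and any outside exercise kept in the other arm. The planned analysis cannot separate them. The limitations in the Discussion cover the missing active control but not this point.

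**Working it through.** **1. What the text allows**

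| | Exercise arm | Waiting-list arm |
|---|---|---|
| Study workouts | 12 over four weeks | none |
| Gym use outside the study | no instruction stated | asked not to |
| Joining an exercise programme | no instruction stated | asked not to |
| Habitual exercisers eligible | yes | yes |

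Randomization balances exercise habit in expectation, but the instruction acts after allocation, so that balance does not cancel it. The ANCOVA covariates (baseline score, sex, age category) do not include exercise. Adding baseline habit would not cure the problem either, because the instruction itself differs by arm.

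**2. The plan's own figure**

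Inputs from the Sample size section: η² = 0.14, 80% power, two-sided 5%, three covariates, 20% drop-out.

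- f² = 0.14 / (1 − 0.14) = 0.1628, so f = 0.403. For two equal arms d = 2f = 0.807 SD.
- Noncentral F with 1 and N − 5 degrees of freedom and noncentrality N·f²: N = 50 gives power 0.797 and N = 51 gives 0.805, so 51 completers are needed.
- 51 / (1 − 0.20) = 63.75, rounded up to 64, or 32 per arm. The stated size is reproduced, and this point does not alter it.

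**3. Possible size of the shift**

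The article gives neither the share p of habitual exercisers nor the loss e (in residual SD of Stroop change) from a four-week pause. Both are assumptions here. If only the controls' pause matters, the shift relative to a usual-activity comparison is b = p × e.

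If the programme added nothing over usual activity, the chance of P < 0.05 follows from the noncentral F with 1 and 46 degrees of freedom and noncentrality 51 × (b/2)²:

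| p | e (SD) | b (SD) | b / 0.807 | 51 × (b/2)² | Chance of P < 0.05 |
|---|---|---|---|---|---|
| 0.1 | 0.2 | 0.02 | 2.5% | 0.005 | 0.051 |
| 0.2 | 0.4 | 0.08 | 9.9% | 0.082 | 0.059 |
| 0.4 | 0.8 | 0.32 | 40% | 1.306 | 0.201 |

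The last row is extreme: it assumes that a four-week pause costs each person almost the whole planned effect of 0.807 SD. With all 64 participants analysed, the middle row gives 0.061 and the last row 0.242.

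**4. Direction**

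If habitual exercisers in the exercise arm replaced their usual sessions with the study workouts and each lost s SD by doing so, the shift would become b = p × (e − s). It vanishes when s = e. Exercise kept or added in that arm would push the other way. A shift towards the programme is the likelier result, but the documents do not settle the sign.

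**The case against.** Four arguments on the other side carry weight.

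- **Guarding against contamination is normal.** Volunteers for an exercise trial may well join a gym while they wait. A comparator without organised exercise is a legitimate choice, the section refers to a non-exercise control group, and the article says openly what controls are asked to do. This stands. A reader might infer that the trial set out to test training added to usual activity and uses the wrong comparator. The documents do not support that: the stated purpose is whether four weeks of combination training can improve cognitive functions, with no mention of usual activity.
- **The exercise-arm half rests on silence.** A condensed article may leave out participant instructions or questionnaire items. This also stands: the article does not show that outside exercise was permitted in that arm or went unrecorded. What remains is a restriction printed under one arm with no stated counterpart.
- **The wording is not clearly an order to stop.** Joining a programme means starting one. Not going to the gym can cover existing use, but existing exercisers are not mentioned, and everyday activity such as walking is not restricted.
- **The size is assumed throughout.** This is correct, and the middle case is close to negligible.

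None of this removes the asymmetry in the stated instructions.

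**Conclusion.** The point holds as a cheap improvement. The article states an arm-specific instruction on outside exercise, leaves habitual exercisers eligible, and plans an analysis that cannot remove a resulting difference. The bias most likely favours the programme and is probably small: about one percentage point on the false-positive rate in the middle case. Across the assumed ranges the rate runs from 5.1% to 20%, with the upper end reached only under extreme values. These figures rest on an assumed share of exercisers, an assumed loss from pausing, and no substitution in the exercise arm.

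A reader might go further and conclude that the contrast is definitely pushed towards the intervention, or that a positive result could not be trusted. The documents do not support either reading, because they give no share of exercisers, no effect of pausing, and no statement on what the exercise arm does outside the study.

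**What to change.** 1. In the allocation letters of both arms, give the same instruction on exercise outside the study workouts. The sponsor should choose, and state in the protocol, whether the comparison is with no organised exercise or with usual activity. Either is defensible if it applies to both arms.
2. Add one question on current gym or class attendance to the existing screening questionnaire and one on outside exercise during the four weeks at post-test. Report both by arm, as description. The post-test answer arises after randomization and should not be added as a covariate to the primary model.
3. If controls keep the present instruction, describe the comparison as training versus being asked to refrain from gym and programme exercise.
4. If the full protocol already gives the exercise arm a matching instruction, the article only needs to say so.

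**Cost:** one sentence in the letters and two questionnaire items, with no change to the sample size. Recruitment was under way, so participants already allocated would have had slightly different instructions from later ones, and the date of the change should be recorded. If usual activity is chosen, some controls stay active and the contrast may be slightly smaller.
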